**(1) Social dominance**			
	Patient-provider talk time	Duration	Linear
	First person plural pronouns	Proportion	Linear
	Turn-taking	Frequency	Poisson
	Interruptions and overlapping speech	Frequency	Poisson
**(2) Interaction anxiety**			
	Anxiety-related words	Proportion	Linear
	Hesitation markers	Proportion	Linear
**(3) Avoidance (Lack of engagement)**			
	Encounter length	Duration	Linear
	Back-channeling responses	Proportion	Linear

#### Topic comprehensiveness of clinical discussion

Next, we will assess the extent to which topics discussed during clinical encounters are consistent with key topics included in the National Cancer Institute’s (NCI) Cancer Genetics Risk Assessment and Counseling (PDQ®)-Health Professional Version [70]. To do this, two genetic counselors on our team will create a topic codebook based on the PDQ®-Health Professional Version. The codebook will provide coding procedures and rules as well as descriptions and examples of each topic. While the codebook is being developed, two coders will unitize the verbatim transcripts into discrete topics or focal ideas/themes. The coders will be first trained on the unitization with a few transcripts before they start unitizing all transcripts. They will meet every 5 transcripts to discuss and solve discrepancies in the identified thought units. After all the verbatim transcripts are unitized into discrete topics, two coders will be trained on the codebook until they achieve consensus and then code all transcripts independently, while meeting every 10 transcripts to discuss discrepancies and reach consensus. We will use consensus estimates for two reasons. Methodologically, discussion topics are discrete categories [71]. Clinically, providers are expected to discuss with patients each topic clearly and with no ambiguity. Finally, for each encounter, we will create dichotomous (a given topic discussed/not discussed) and continuous (the total amount of time spent on discussing a given topic in seconds) outcomes.

We will also explore additional topics beyond those specifically included in the PDQ®-Health Professional Version. To identify these additional topics, the genetic counselors on our team will independently review all units with no assigned codes. Next, they will discuss discrepancies in identified topics and collectively refine and organize them into higher-level categories. We will create an additional topic codebook that only includes topics that were identified by the two genetic counselors but not currently in the PDQ®-Health Professional Version. After being trained on the codebook, two independent coders will code all transcripts independently. Any discrepancy in coding between the two coders will resolved by discussion and reaching consensus. Finally, for each encounter, we will create dichotomous (a given topic discussed/not discussed) and continuous (the total amount of time spent on discussing a given topic in seconds) outcomes.

## Measures

### Genetic counseling provider baseline survey

#### Demographic information

We will assess self-reported age, race, ethnicity, gender, and sexual orientation.

#### Professional information

We will assess status (genetic counselor vs. genetic counseling trainee), years in practice (genetic counselor only), years at the current institution (genetic counselor only), or year in training (genetic counseling trainees only).

#### Prior experience with cultural competency training

Genetic counseling providers will be asked to indicate whether and when they most recently *participated in* as well as *led* training related to cultural competency. Providers who have participated in and/or led such training will be further asked to respond to the following set of four items: [1] the main goal(s) of the most recent training they participated in/led (free text); [2] whether the training was part of their required duties or curriculum (yes/no); [3] whether the most recent training was the first training they have had/led in cultural competency and related topics (yes/no); and [4] approximately how many hours of cultural competency-related training they have completed/led over the last 2 years (in hours). Finally, all providers will be asked to rate their ability to provide culturally competent genetic counseling (1: Poor to 5: Outstanding).

#### Prior experience with communication skills training

Similarly to the assessment of prior experience with cultural competency training, genetic counseling providers will first be asked to indicate whether and when they participated in and/or led communication skills training most recently. Those who have participated in and/or led communication skills training will be further asked to respond to the following set of four items: [1] the main goal(s) of the most recent training they participated in/led (free text); [2] whether the training was part of their required duties or curriculum (yes/no); [3] whether the most recent training was the first communication skills training they have had/led (yes/no); and [4] approximately how many hours of communication skills training they have completed/led over the last 2 years (in hours). All providers will be also asked to rate their communication skills (1: Poor to 5: Outstanding).

#### Prior experiences with Black patients

We will assess genetic counseling providers’ prior experiences with Black patients with two items: [1] how often they meet with Black patients in their practice or as part of their training (1: Never to 6: All the time); and [2] how they would rate their communication skills with Black patients (1: Poor to 5: Outstanding).

#### Implicit racial prejudice

Implicit racial prejudice will be assessed with the well-validated Race Implicit Association Test (Race IAT) [72, 73]. Individuals classify items into four categories: two racial groups (White vs. Black) and two evaluations (good vs. bad), which are presented in pairs. Participants respond more quickly when the racial group and evaluations mapped onto the same response are strongly associated than when they are weakly associated. In the Race IAT, two racial groups are represented by 12 photographs of faces, and two evaluative categories are represented by 16 words (8 good words: marvelous, superb, pleasure, beautiful, joyful, glorious, lovely, wonderful; and 8 bad words: tragic, horrible, agony, painful, terrible, awful, humiliate, and nasty). The Race IAT is scored by computing a *D* score that ranges from − 2.0 to 2.0 (the interitem consistency mean *α’*s = 0.78) [74].

#### Explicit racial prejudice

We will use a widely-used, well-validated “feeling thermometer,” [75] in which participants rate their feelings toward certain social groups using a scale ranging from 0 (very cold) to 100 (very warm) [76]. We will create composite explicit pro-White/anti-Black prejudice scores, which mirror *D* scores in the IAT, by subtracting a score for Black Americans from a score for White Americans. Greater positive values indicate explicit preference for White Americans over Black Americans while greater negative values indicate explicit preference for Black Americans over White Americans. A value of zero indicates no explicit preference between Black and White Americans.

#### Implicit racial stereotyping

Implicit racial stereotyping will be assessed with the medical cooperativeness IAT, the commonly used implicit measure of racial stereotyping in racial health disparities research [77, 78]. The task is the same as the Race IAT except that two evaluative categories (good vs. bad) are replaced by two stereotyping categories (medically cooperative vs. medically uncooperative). More specifically, 16 words that are to be categorized into evaluations (good vs. bad) are replaced by 12 words that are to be categorized into stereotypes (6 words associated with cooperativeness: willing, cooperative, compliant, reliable, adherent, helpful; and 6 words associated with uncooperativeness: reluctant, doubting, hesitant, apathetic, resistant, and lax). *D* scores will be computed using the same algorithm as for the Race IAT. Greater positive values indicate implicit association of White (vs. Black) Americans with medical cooperativeness, while greater negative values indicate implicit association of Black (vs. White) Americans with medical cooperativeness.

#### Explicit racial stereotyping

Genetic counseling providers will be asked to complete a 32-item measure that is designed to assess racial stereotypes in general (16 items for Black Americans, and 16 items for White Americans; e.g., unintelligent, lazy, low socioeconomic status) and a 34-item measure that is designed to assess stereotypes specifically in the medical context (17 items for Black Americans, and 17 items for White Americans; e.g., medical cooperativeness, health literacy, motivation), [21] which were adapted from previous studies of racial stereotyping [31–34]. In both measures, genetic counseling providers will be instructed to read statements and indicate the extent to which each statement describes characteristics of Black vs. White Americans, on a Likert scale that ranges from 1 (very untrue) to 6 (very true). Following the procedure used in prior research, a composite score will be computed for each general- and medicine-specific stereotype. Specifically, we will first reverse-code negatively worded items and compute the average score for each racial category. Next, we will subtract the average score for Black Americans from the average score for White Americans. Greater positive values indicate explicit association of White Americans (vs. Black Americans) to more positive stereotypes, while greater negative values indicate explicit association of Black Americans (vs. White Americans) to more positive stereotypes.

### Patient baseline survey

#### Demographic information

We will assess self-reported age, race, ethnicity, gender, pronouns they use, sexual orientation, U.S. citizenship, height and weight (to compute BMI), lifestyle cancer risk factors (e.g., smoking, alcohol use, physical activity), marital status, education, income, the number of people in household, personal and family cancer history, health insurance, and lifestyle behaviors (e.g., diet, physical activity, smoking, and alcohol consumption).

#### Perceived racial discrimination

Patients will be asked to complete two well-validated measures of perceived racial discrimination that have been used in health research and social psychology research previously. The first is the Brief Perceived Ethnic Discrimination Questionnaire-Community Version (*α* = 0.87) that assesses both daily and lifetime experience of multiple forms of discrimination (e.g., exclusion, stigmatization, threat) in multiple domains (e.g., work, public places) [79]. Participants will be asked to use a scale ranging from 1 (Never) to 5 (Very often). The second measure assesses the perceptions of racial discrimination at both personal and group level [80, 81]. More specifically, five items are designed to assess the degree to which patients have experienced discrimination personally (*α* = 0.84), and three items are designed to assess the degree to which patients perceive other members of their racial group in general experience racial discrimination (*α* = 0.84). Both subscales will be assessed by using response items that range from 1 (Strongly disagree) to 5 (Strong agree).

#### General trust in genetic counselors

We will assess patients’ expectation about their trust in general counselors within the specific health system with a modified version of the Wake Forest Physician Trust Scale, which has been found to have better internal consistency (*α* = 0.93, test-retest reliability = 0.75), validity, discriminability, and scale distribution as compared to other trust scales [82, 83]. To account for patients having never met with a genetic counselor, they will be instructed to indicate how they expect to feel regarding trust in their counselor. The response items will range from 1 (Strongly disagree) to 5 (Strongly agree).

#### General satisfaction with healthcare

We will use a modified version of the Patient Satisfaction Questionnaire Form III [84] to assess patients’ satisfaction with the specific *healthcare system* in general, as opposed to satisfaction with genetic counselors within the specific healthcare system, because the vast majority of patients will have had no prior experience with genetic counselors. In Particular, we will use three subscales: general satisfaction (*α* = 0.88), interpersonal aspects (*α* = 0.82), and communication (*α* = 0.82). The response items will range from 1 (Strongly disagree) to 5 (Strongly agree).

#### Perceived empowerment

We will assess perceived empowerment with the Genomics Outcomes Scale (GOS) [85]. The GOS is a six-item scale measuring patient empowerment following genetic counseling. This scale was derived from and is highly correlated (*r* = .84) with the longer Genetic Counseling Outcomes Scale [86]. The response items range from 1 (Strongly disagree) to 5 (Strongly agree).

#### Perceptions of genetic testing

Patients will complete the 14-item Attitudes Toward Genetic Testing (ATGT) scale (*α* = 0.73) [87]. It assesses perceptions of anxiety/conflict, discrimination, risk information, and prevention/surveillance relevance of cancer genetic testing and is suitable for providers, patients, and the general public. Again, the response items range from 1 (Strongly disagree) to 5 (Strongly agree).

#### Decisional conflict

Patients will complete a 16-item Decisional Conflict Scale (DCS) (*α* = 0.78 to 0.92), [88] modified for the context of hereditary cancer testing. The scale captures patients’ uncertainty about their genetic test decision, what factors contribute to that decision, and how effective they perceive they are in making a decision. Again, the response items range from 1 (Strongly disagree) to 5 (Strongly agree).

### Genetic counseling provider post-encounter survey

#### Therapeutic alliance

We will assess a provider’s perception of the strength of the relationship with a patient using the Working Alliance Inventory-Short Form Revised (WAI-SR) (Therapist). This 12-item measure assesses three domains: goals of the genetic counseling session, tasks to achieve those goals, and bond between the provider and patient. The WAI-SR has high internal consistency (*α* = 0.91) and correlates well with other measures of therapeutic alliance [89]. The response items will range from 1 (Strongly disagree) to 5 (Strongly agree).

#### Decision about genetic testing

Genetic counseling providers will be asked to indicate whether their patient made a decision about genetic testing during the genetic counseling session using the following options: [1] yes, and they decided to take genetic testing; [2] yes, and they decided not to take genetic testing; [3] no, they need more time to think about it; and [4] no, I did not offer genetic testing.

### Patient post-encounter survey

#### Decision about genetic testing

Patients will be asked to indicate whether they made a decision about genetic testing during the genetic counseling session using the following options: [1] yes, and I decided to take genetic testing; [2] yes, and I decided not to take genetic testing; [3] no, I need more time to think about it; and [4] no, I was not offered genetic testing.

#### Therapeutic alliance

Similarly to genetic counseling providers, the patient’s perception of the strength of the relationship with a genetic counseling provider will be assessed with WAI-SR (Client) [89].

#### Provider-specific trust

We will assess patient trust in the specific genetic counseling provider they have just met with a modified version of the Wake Forest Physician Trust Scale [83]. Items will be modified to reflect the specific provider a patient saw during their encounter.

#### Provider- and encounter-specific satisfaction

Patient satisfaction with the specific genetic counseling provider they have just met as well as with the counseling session they have just completed will be assessed with the 6-item Genetic Counseling Satisfaction Scale (GCSS) using a 5-point scale ranging from 1 (Strongly disagree) to 5 (Strongly agree). The GCSS assesses the extent to which patients feel the encounter was valuable and whether the provider understood the patient’s concerns. It has demonstrated excellent reliability (*α* = 0.90) among breast cancer genetic counseling patients [90] and has been used recently to assess satisfaction among Black patients [91] as well as patients receiving telegenetic counseling [92].

#### Perceived empowerment

We will use the same GOS [85] as in the patient baseline survey to assess perceived empowerment.

#### Perceptions of genetic testing

Perceptions of genetic testing will be assessed with the same ATGT scale [86] as in the patient baseline survey.

#### Decisional conflict

Patients’ decisional conflict related to hereditary cancer testing will be assessed with the same DCS [88] as in the patient baseline survey.

Aim 1 (to compare/contrast the nature of patient-provider communication by patient race) examines Path A in our conceptual model. To test Path A, first, we will examine a numerical and graphical summary of descriptive statistics that will inform the distribution of the 15 outcomes (14 categorical variables and the overall patient-provider communication) and that may require data transformation. Then, we will conduct two separate analyses for communication and linguistic patterns. To examine how genetic counseling providers’ communication style differs by patient race, we will identify covariates by conducting bivariate correlations among all 15 outcomes and factors that were assessed in the baseline surveys (e.g., provider/patient demographics including sex, provider professional characteristics, patient perceived discrimination). Next, we will estimate a linear regression model for each outcome with the main effect of patient race, the main effect of care modality, a two-way interaction between patient race and care modality, and covariates identified as highly correlated with the outcomes. We will use GEE (which controls for the dependence in outcomes due to patients nested within providers) in these regressions, instead of multilevel modeling (which models the nonindependence in data), because there will not be enough upper-level units (i.e., counselors) to model random effects in our data. We will use the Bonferroni correction [93, 94] to address family-wise errors due to multiple comparisons. To examine which specific linguistic patterns differ by patient, we will conduct analyses in similar steps described above. First, we will identify highly correlated covariates by computing bivariate correlations among all quantified linguistic patterns and factors assessed in the baseline surveys. Next, we will conduct a regression for each quantified linguistic pattern with the main effect of patient race, the main effect of care modality, a two-way interaction between the two, and covariates using GEE and the Bonferroni correction. Type of regressions will depend on the measurement units.

Aim 2 (to compare/contrast the clinical discussion content by patient race) examines Path B in our conceptual model. We will examine which topics significantly differ between Black and White patients. First, we will identify covariates that may impact clinical discussion content by computing bivariate correlations among all topics and factors assessed in the baseline surveys. All significant factors will be included in the main analyses as covariates. In the main analyses, we will conduct a logistic regression (the dichotomous outcome) and a linear regression (the continuous outcome) for each topic with the main effect of patient race, the main effect of care modality, a two-way interaction between the two and covariates using GEE and the Bonferroni correction.

Aim 3 (to quantify the role of each type of counselor bias in patient-provider communication and clinical discussion content) examines Paths C and D in our conceptual model. Analyses will be carried out in three steps. In Step 1, we identify covariates associated with patient-provider communication or clinical discussion content. We will compute correlations among all facets of patient-provider communication/clinical discussion topics identified in Aims 1 & 2 and factors assessed in the baseline surveys (e.g., provider/patient demographics, provider professional characteristics, patient perceived discrimination). In Step 2, we compute partial correlations between all forms of provider bias and aspects of patient-provider communication/clinical discussion topics identified in Aims 1 & 2, controlling for covariates that were significantly associated with any of the provider behaviors. In Step 3, we conduct two regressions for each of the specific aspects of patient-provider communication and clinical discussion topics that remain statistically significant in Step 2. One regression will focus on the role of provider prejudice and will consist of four main effects (patient race, provider implicit prejudice, provider explicit prejudice, care modality), all six combinations of two-way interactions, all four combinations of three-way interactions, and one four-way interaction among all predictors. The second regression model will focus on the role of provider stereotyping and will consist of four main effects (patient race, provider implicit stereotyping, provider explicit stereotyping, care modality), all six combinations of two-way interactions, four combinations of three-way interactions, and one four-way interaction among all predictors. The type of each outcome, summarized in Table 4, will determine the regression model to analyze. The regressions will also include the same set of covariates as in Step 2. All four types of provider bias will be grand-mean-centered. We will use GEE and the Bonferroni corrections in analyses. The provider communication styles that remain statistically significant in Step 3 are considered as key communication styles that contribute to racial disparities in the cancer genetic counseling process and reflect provider bias.

**Table 4 Tab4:** An overview of the outcomes and analyses for each aspect of patient-provider communication and clinical discussion content

Outcome types	Variables	Analytical approaches
Continuous: Likert scale	*Patient-provider communication* (Provider communication style; The overall quality of patient-provider communication)	Linear regression with GEE
Continuous: Frequency	*Patient-provider communication* (Each type of silence; Each type of adjacency pairs; Each type of problems)	Poisson regression with GEE
Continuous: Proportion	*Patient-provider communication* (Topics initiated by providers; Primary units allocated to providers; Silence followed by provider talks; Repairs initiated by providers; Problems repaired by providers)	Linear regression with GEE
Continuous: Duration	*Patient-provider commu*nication (Each type of silence) *Clinical discussion con*tent (The amount of time spent on discussing a given topic)	Linear regression with GEE
Dichotomy	*Clinical discussion content* (The presence/absence of a given discussion topic)	Logistic regression with GEE
Multiple categories	*Patient-provider communication* (The primary units of turns)	Multinomial logistic regression with GEE

Finally, Aim 4 (to quantify the impact of patient-provider communication/clinical discussion content with patient-centered outcomes) examines Paths E and F in our conceptual model. The analyses will be carried out in steps similar to those in Aim 3. In Step 1, we will identify covariates associated with patient-centered outcomes by computing correlations among all aspects of patient-provider communication/clinical discussion topics and factors assessed in the patient baseline survey, the provider baseline survey, and the provider post-encounter survey. In Step 2, we will compute partial correlations between all aspects of patient-provider communication/clinical discussion topics identified in Aims 1 and 2 and patient-centered outcomes while controlling for covariates identified in Step 1. In Step 3, we will conduct a linear regression with GEE and Bonferroni correction for each self-reported outcome (e.g., trust, satisfaction, therapeutic alliance) and a logistic regression with GEE for behavioral outcome (genetic testing completion). All regressions will include the same set of predictors (aspects of patient-provider communication/clinical discussion topics that remain significant in Step 2, and care modality) and covariates. Aspects of patient-provider communication/clinical discussion topics that remain significant in Step 3 are considered as potentially important intervention points for reducing racial disparities in patient-centered outcomes.

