## Background

Individuals with cancer are more likely to die from it if they are Black, [1] although hereditary cancer is distributed similarly across race [2, 3]. Because prevention is key to the cost-effective and long-term control of cancer, [4] the potential for cancer genetic counseling to play a central role in reducing racial cancer disparities is high. Genetic counselors address the medical, psychological, and familial concerns related to genetic disease, [5] including hereditary cancer. Yet, the benefits of genetic counseling are not equitable across race. Studies continue to show that Black patients with breast or colon cancer are less likely to discuss genetic evaluation or genetic counseling referral with their providers [6–8]. A systematic review also revealed racial disparities in genetic counseling experiences [9]. Despite a rapidly increasing discourse about, and recognition of, potential racial disparities in the genetic counseling process, only one study, to our knowledge, has directly compared Black and White patients [10]. In that study, Black women with breast cancer who had genetic counseling were less likely to have genetic testing. But, what happened during the genetic counseling session that may have led to this disparity was not examined.

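### Aim 1 admits baseline factors to the race models only if highly correlated with the outcomes, so moderate confounding by cancer history can stay in the Black-White contrast

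*Protocol article*

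**What the plan says.** In the Protocol article, Statistical analysis, Aim 1 first screens for covariates: "we will identify covariates by conducting bivariate correlations among all 15 outcomes and factors that were assessed in the baseline surveys". Each global-affect model then contains "the main effect of patient race, the main effect of care modality, a two-way interaction between patient race and care modality", plus the "covariates identified as highly correlated with the outcomes". The linguistic patterns are handled the same way: "we will identify highly correlated covariates by computing bivariate correlations among all quantified linguistic patterns and factors assessed in the baseline surveys". No numerical threshold is attached to either screen, and no clinical factor is fixed in advance.

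The neighbouring aims are worded differently. Aim 2 states: "All significant factors will be included in the main analyses as covariates". Aim 3 (Step 2) controls for the covariates that reach significance against any one of the provider behaviours.

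The patient baseline survey (Demographic information) collects "personal and family cancer history". Under Participants, eligibility requires an appointment about a hereditary cancer condition. It does not separate affected from unaffected patients and does not restrict family history. The design aims for similar numbers of Black and White patients within each provider and does not match on clinical history.

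**The concern.** Confounding of the race contrast is the product of two things: how far a factor differs by race, and how strongly it affects the outcome. The Aim 1 screen looks only at the second and, read literally, asks for a high value of it. A factor with a modest effect on communication but a clear race difference is then left out, although it can produce an apparent Black-White gap or hide a real one.

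Cancer history is the obvious candidate. Whether the patient already has cancer, and what the family history is, can reasonably alter the length and tone of a pre-test session whatever the provider's attitude. The Background reports that "Black patients with breast or colon cancer are less likely to discuss genetic evaluation or genetic counseling referral with their providers", which makes it plausible that the mix of patients reaching counseling differs by race.

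At stake is the reading of Path A. A difference due to clinical history could be reported as a difference in how providers communicate. Aims 3 and 4 also work from the aspects identified in Aims 1 and 2, so an error here affects what is carried forward.

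**Working it through.** The plan states no figure on this point. The check is a reading of the rule followed by an illustration of its size.

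**Inputs from the Protocol article**
- 220 patients, about equal by race, so about 110 v 110.
- 15 global-affect outcomes with Bonferroni correction. Alpha is not stated; 0.05 two-sided is assumed, giving 0.05/15 = 0.0033 per test.
- The sample-size paragraph treats d = 0.2 as the effect to detect. That figure is for provider implicit prejudice, not patient race, and serves here only as a yardstick.

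**Inputs assumed, because the documents do not give them**
- Two factors (personal and family history), independent within race and acting in the same direction.
- Each differs by race by 0.3-0.5 SD and has an outcome slope of 0.15-0.20 SD.
- No true race effect. Ordinary least squares, without provider clustering or the modality terms.
- Highly correlated is read in turn as |r| at least 0.5, |r| at least 0.3, and p<0.05.

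**Step 1: would such factors pass the screen?** With gap g and slope b, the covariance of one factor with the outcome is b(1 + g²/4) + b·g²/4, and the factor's SD is √(1 + g²/4). The outcome SD is about 1.
- g = 0.3, b = 0.15: 0.157/1.011, so r is about 0.16.
- g = 0.5, b = 0.20: 0.225/1.031, so r is about 0.22.

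With 220 patients, p<0.05 corresponds to |r| of about 0.13. These factors would usually pass a significance screen and usually fail a bar of 0.3 or 0.5.

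**Step 2: bias when both are left out.** Bias = 2 × g × b. The standard error of the race contrast is √(2/110) = 0.135. Type I error = Φ(bias/SE − z) + Φ(−bias/SE − z), with z = 1.96 at 0.05 and 2.935 at 0.0033.

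| Gap (SD) | Slope (SD) | Bias (SD) | Error at 0.05 | Error at 0.05/15 |
|---|---|---|---|---|
| 0.3 | 0.15 | 0.09 | 10% | 1.2% |
| 0.3 | 0.20 | 0.12 | 14% | 2.1% |
| 0.5 | 0.15 | 0.15 | 20% | 3.4% |
| 0.5 | 0.20 | 0.20 | 32% | 7.3% |

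Simulation of the size-bar rules agrees: about 0.09-0.20 SD, 10-31% at 0.05, and 1-7% at 0.05/15. The bar of 0.5 behaves as if nothing were adjusted. The bar of 0.3 is somewhat milder.

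**Step 3: the alternatives.** With both factors always in the model, type I error is about 5%. With entry at p<0.05, the residual bias is about 0.01 SD, and no more than about 0.03 SD in any scenario checked.

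**Step 4: a second parameterisation.** Take one binary history variable with 50% overall prevalence (SD 0.5). The outcome difference by history is 2r, so bias = 2 × r × prevalence gap. For r = 0.3 and gaps of 10, 20 and 30 points, bias is 0.06, 0.12 and 0.18 SD. Under a bar of 0.5, simulated type I error is 7%, 14% and 26%. Under a bar of 0.3, bias falls to about 0.03, 0.05 and 0.07 SD, because history then enters in about half of the datasets.

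**The case against.** The strongest reply is that the harm depends on a cut-off the article never states. The nearby screens use significance, and if Aim 1 means the same, the residual bias is negligible. An article may also leave a threshold to the fuller plan. This stands as a limit on the size. It does not remove the point, because the words chosen for Aim 1 differ from those of Aims 2 and 3 and ordinarily mean more than significant.

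A reader might infer more than the documents support in four ways.
- *That the race mix of histories is known to differ.* The Background statement concerns discussion of evaluation and referral. It says nothing about affected status or family history among patients who reach counseling.
- *That some outcomes will be adjusted and others not.* The screen refers to the outcomes in the plural, so one common covariate set is an equally open reading. Under it, with 15 outcomes at an assumed residual correlation of about 0.5 and the largest gap and slope, the bar of 0.3 leaves about 0.11 SD and 15% error, against about 0.18 SD and 26% outcome by outcome. The bar of 0.5 gives the same result either way.
- *That bias near 0.3 SD, with error of about one half, is in play.* That needs three factors pulling the same way and no multiplicity correction. Only two are at issue, and Bonferroni is planned.
- *That Aims 2 and 3 share the defect.* Their significance rules are nearly harmless on this calculation, and Aim 3 already keeps any factor significantly associated with any provider behaviour. That does not, however, undo what Aim 1 has selected.

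**Conclusion.** The point holds for Aim 1, for both the global-affect and the linguistic models. The stated rule selects covariates by strength of outcome correlation alone, sets an undefined but seemingly high bar, and fixes no clinical factor. Eligibility and the within-provider balance of race do not compensate.

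The size is conditional on three things: a size-type reading of the rule, a race gap in history, and an effect of history on communication. The documents quantify none of them. Under the stated assumptions the largest bias equals the d = 0.2 used as the sample-size yardstick. Bonferroni lowers the error rate but does not remove the bias: 1-7% per test is about 3 to 21 times the nominal 0.33%. This should be corrected, but it does not undermine the study.

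**What to change.** Include personal cancer history (affected or unaffected) and family cancer history in every Aim 1 model, whatever their correlation with the outcome. State that no correlation-size cut-off will be used to exclude them. These are clinical facts that precede the encounter, unlike perceived discrimination, which may be part of the disparity itself. If a screen is kept for the remaining factors, state its threshold and whether it yields one common set or one set per outcome.

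Using the same two fixed terms in Aim 2 is optional, for consistency. Aim 3 needs no change on this account.

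The cost is a change of wording and two or three patient-level degrees of freedom per model. The data are already to be collected.
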